## Methods/Design

We hypothesize thatUse of clean cookstoves introduced before the third trimester of pregnancy will lead to a significant increase in average birth weight.Use of clean cookstoves starting before the third trimester of pregnancy will lead to a significant reduction in the risk of physician-assessed severe pneumonia within the first year of life.

We are testing these hypotheses in a cluster-randomized intervention trial involving 1225 maternal-infant pairs in the Kintampo North and South districts of Ghana, West Africa. Thirty-five rural communities were randomly assigned to one of two intervention arms, or to a control arm. Community-based fieldworkers identify pregnant women and enroll them into the study. Gestational age is determined via ultrasound (SonoSite Inc., Bothel, WA, USA) at the enrollment clinic visit [16].

In intervention communities, we distribute intervention cookstoves to pregnant women after enrollment, along with health insurance and an insecticide-treated bed net. The control group receives insurance and an insecticide-treated bed net at enrollment, and an efficient biomass cookstove at the completion of the postnatal follow-up period in the matched intervention communities. We assess real-time personal exposure to CO among all studied participants during pregnancy (four times each) and among the infants during the first year of life (three times each). We monitor subsets of mothers during pregnancy (once) and of the infants (once) for real-time and PM_2.5_ during one of the CO monitoring sessions.

We measure birth weight to the nearest gram using a Tanita BD 585 digital baby scale (Tokyo, Japan). We record the time elapsed between delivery and birth weight measurement, and only birth weights collected within 24 hours of delivery are considered valid. Birth length and head circumference are also measured, and a placental sample is collected for malaria assessment and archiving. Birth measures are obtained for both health facility and home births.

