**Fig. 2 Fig2:**
[figure not shown]
Flow chart

In the efficient biomass cookstove arm – hereafter called the “BioLite arm” – households receive two BioLite HomeStove cookstoves (BioLite Inc., Brooklyn, NY, USA). These stoves burn freely available biomass fuels, but do so in a constrained L-shaped combustion chamber that increases heat transfer efficiency relative to traditional three-stone fires (more energy to the pot per unit of wood). In addition, a fan blows air into the combustion chamber, which improves the combustion efficiency of the system. A thermoelectric generator powers the fan, enabling use without a connection to an electrical grid. While some versions of the BioLite provide power via a Universal S Bus (USB) port, we opted for a version that optimizes combustion efficiency at the expense of USB power.

Study participants in the LPG arm receive a two-burner LPG stove manufactured in Ghana by the Ghana Cylinder Manufacturing Co. (Accra, Ghana). We chose that particular stove because it is readily available in Ghana, both for the current study and for potential future distribution. Enrolled households also receive timely deliveries of LPG gas at no cost to the participants. GRAPHS leased a 5000-kg LPG tank to ensure continuous supply. If households run low on LPG prior to a scheduled delivery, they can contact their fieldworker and the study will make a special delivery. Control arm participants use their own three-stone traditional stoves for the duration of the trial and will receive one BioLite stove at the end of the study period. All participants receive an insecticide-treated net (ITN).

Community-based fieldworkers visit households every week to check up on the intervention stoves and address any problems. In the control areas the community-based fieldworker visits take place as in the intervention arms, and are framed as checkups on the ITNs.

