### Analysis plan

We plan to evaluate the impact of the interventions on birth weight and pneumonia using two methods. First, we will carry out intention-to-treat analyses for both birth weight (assessed as a continuous variable: grams at birth) and incidence of physician-assessed severe pneumonia (assessed as new cases per weeks of child observation). Second, we will carry out exposure-response analysis in which we pool data across arms and model how our outcome variables are related to exposure levels. We will use non-linear models that account for confounders and for clustering. Missing data will be imputed using standard multiple imputation techniques [30]. Both analyses will be carried out with and without adjustments for covariates. In particular, we will control for mother, household, and community characteristics. In the case of birth weight, we will also control for placental malaria.

In addition to these main analyses, we plan several subgroup analyses on our primary outcomes, including comparison of groups defined on residence type (compound versus freestanding households); proximity to main road; gestational age at recruitment; and density of other exposure sources. We also plan to carry out secondary analyses on other birth and health outcomes that we predict will respond to reduction in air pollution exposure.

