We also started investigating an LPG intervention. LPG is very clean [33] and very convenient, but we were uncertain of its public health relevance given its high cost and limited availability in Ghana. In 2012 we learned, however, that Ghana had laid plans for a substantial program to increase access to LPG both in rural and urban areas [34] and that Ghana’s Ministry of Energy had initiated a “Rural LPG Program” that was delivering free cookstoves and subsidized gas to rural communities. This support from the government was sufficient to convince the GRAPHS team that LPG was indeed a germane alternative.

We remained convinced, however, of the need to include an efficient biomass arm. While our interactions with the Government of Ghana had persuaded us that LPG was worth testing, we remained hopeful that efficient biomass combustion would provide a substantially less costly intervention for future large-scale interventions. Between 2010 and 2012 BioLite developed a production model of their HomeStove, and we began pilot testing in spring 2012. Initial units proved unreliable, but after several iterations we were satisfied that the BioLite was robust to long-term use. We launched enrollment in fall 2013 when the first shipment of BioLite stoves reached our study area in Ghana.

Our intervention entails providing participating households with clean cookstoves and, in the case of the LPG intervention, with an adequate supply of fuel. As with many public health interventions, we cannot ensure perfect compliance. While we try to minimize use of the traditional three-stone fires in intervention households through weekly stove use encouragement visits, we have observed that many households continue to use traditional stoves for certain cooking tasks (a practice sometimes referred to as “stove stacking” [35]). We address this in three ways. As discussed below, we are currently undertaking a separate study to objectively quantify stove use across arms and to link it to household characteristics. Additionally, we carry out weekly questionnaire-based assessments of stove use; these data will be available as a covariate in our adjusted analyses of our main health outcomes. Third, we collect extensive personal exposure data, which capture emissions both from continued use of incumbent stoves and from other nearby sources. These data will be used to estimate exposure-response relationships for our main outcomes.

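### The adjusted intention-to-treat analysis of birth weight controls for placental malaria, and the text leaves room for weekly stove use; both arise after randomisation, so the adjusted estimate is not the effect of assignment

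*Protocol article*

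**What the plan says.** The Analysis plan section of the protocol article names two methods, intention-to-treat and exposure-response, for birth weight and severe pneumonia. It then states: "Both analyses will be carried out with and without adjustments for covariates". The adjustment set is maternal, household and community characteristics, and for one outcome there is an addition: "In the case of birth weight, we will also control for placental malaria". Nothing limits that addition to the exposure-response model.

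On timing, Methods/Design says of the intervention communities that "we distribute intervention cookstoves to pregnant women after enrollment", and among the birth measurements that "a placental sample is collected for malaria assessment and archiving".

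The section on selecting intervention cookstoves lists three responses to continued use of traditional stoves. The first is a separate study of stove use. The second is that "we carry out weekly questionnaire-based assessments of stove use", and "these data will be available as a covariate in our adjusted analyses of our main health outcomes". The third is the personal exposure data, of which it says: "These data will be used to estimate exposure-response relationships for our main outcomes". On the control arm, the Interventions section says: "Control arm participants use their own three-stone traditional stoves for the duration of the trial".

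**The concern.** Randomisation balances what exists before the stoves arrive. It does not balance what happens afterwards. An intention-to-treat model that conditions on a later variable which the arm may have changed removes the part of the effect that runs through that variable. It also admits confounding by anything that drives both the variable and the outcome. The result is at best a direct effect under untestable assumptions.

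- **Stove use** is the route by which the intervention is meant to work, and it is strongly tied to arm.
- **Placental malaria** has a weaker link to arm. Every participant gets a treated net, but the weekly visits are stove checks in the intervention arms and are presented as net checks in the control arm. An arm difference in net use, and so in malaria, is possible. The article does not claim one.

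At stake is the reading of the adjusted companion estimate: for birth weight through malaria, and for both main outcomes if stove use enters.

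**Working it through.** **1. Order of events.** Eligibility ends at 24 weeks' gestation so that the stove is in use by 28 weeks. For a birth at 37 weeks (assumed) that leaves at least 37 − 28 = 9 weeks of use before the placenta is sampled. Stove use is recorded weekly during follow-up. Neither variable is a baseline value.

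**2. Scale: the plan's own birth-weight figures.** Inputs from Power calculations: effects of 0.32 SD (BioLite) and 0.40 SD (LPG), intraclass correlation 0.07, n = 455, 455 and 315, stated power 0.82 (BioLite) and 0.84 (LPG). With 1225/35 = 35 women per cluster, the arms would hold 13, 13 and 9 clusters (derived, not stated).

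SE = √[(0.07 + 0.93/35)(1/J₁ + 1/J₂)]

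- BioLite: √[0.0966 × (1/13 + 1/13)] = 0.122, and 0.32/0.122 = 2.63.
- LPG: √[0.0966 × (1/13 + 1/9)] = 0.135, and 0.40/0.135 = 2.97.

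Two-sided power from the noncentral t is 0.71 (BioLite) and 0.81 (LPG). A two-sided normal approximation gives 0.75 and 0.84; a one-sided t gives 0.82 and 0.89. No single variant tried returns both stated figures. Sidedness and clusters per arm are not stated, so this does not show that they are wrong, and nothing below depends on it.

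**3. Placental malaria.** Shift in the arm effect ≈ prevalence difference × effect of infection. The article gives neither, so both are assumed.

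- 3 points and 0.2 SD: 0.03 × 0.2 = 0.006 SD.
- 10 points and 0.4 SD: 0.10 × 0.4 = 0.04 SD, which is 12.5% of 0.32, 10% of 0.40, and about a third of the BioLite SE (0.04/0.122).
- No arm difference: zero.

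A simulation of the LPG comparison (infection effect −0.3 SD, control prevalence about 35%, with and without a common cause of malaria and birth weight) agrees. Adjustment moved the estimate by 0.03 to 0.04 SD at a 10-point difference, in either direction, and by less than 0.001 SD at no difference.

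**4. Stove use, if entered.** If a share m of the effect runs through use, use is reported without error, and nothing confounds use and birth weight, the adjusted arm coefficient tends to (1 − m) × effect. Two-sided t power, with the SE held at its unadjusted value:

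| m | LPG effect | LPG power | BioLite effect | BioLite power |
|---|---|---|---|---|
| 0 | 0.40 | 0.81 | 0.32 | 0.71 |
| 25% | 0.30 | 0.56 | 0.24 | 0.47 |
| 50% | 0.20 | 0.29 | 0.16 | 0.24 |
| 75% | 0.10 | 0.105 | 0.08 | 0.09 |

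The SE would not hold. In a simulation with assumed mean use of the new stove of about 80% in the intervention arm and 3% in controls, the spread of the arm estimate rose from about 0.13 to 0.27 SD (LPG) and from about 0.12 to 0.23 SD (BioLite). Mean estimates fell to 0.20 and 0.17 with half the effect through use, and to −0.03 and 0.01 with all of it.

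**5. How firm a sign reversal is.** Take the BioLite effect as running wholly through use: mean use 0.70 in the intervention arm and 0 in controls, so 0.32/0.70 = 0.457 SD per unit of use. Let use rise by 0.15 per SD of motivation, plus noise of SD s, and let motivation add 0.1 SD to birth weight. The adjusted arm coefficient is then

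−0.70 × (0.1 × 0.15)/(0.15² + s²) = −0.0105/(0.0225 + s²).

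- s = 0.1: −0.32. Motivation and use then correlate at 0.15/√0.0325 = 0.83.
- s = 0.2: −0.17.
- s = 0.3: −0.09.

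With V = 0.0225 + s² and reporting error of SD e, the coefficient becomes 0.32 − 0.70 × (0.457V + 0.015)/(V + e²). At s = 0.1 this is +0.03 for e = 0.2 and +0.15 for e = 0.3.

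The simulation in step 4 gives about −0.42 when a 0.1 SD common cause is added, but there that cause alone determines use within the intervention arm.

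**The case against.** The strongest reply is that the randomised comparison is safe, because the unadjusted intention-to-treat analysis is planned for both outcomes. That stands. A reader might infer that the plan could erase the effect of assignment; the document does not support this, since only the adjusted companion is exposed.

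Second, stove use is not in the Analysis plan section. It appears only in the Discussion, as data that will be available, and the adjusted analyses mentioned there could mean the adjusted exposure-response models. This also stands in part: the text does not commit to stove use in the intention-to-treat models. But it does not keep it out either. The Analysis plan adjusts both methods, and the Discussion gives exposure-response modelling to the personal exposure data as a separate item. Nor does the article say how use would be coded. If the variable is traditional-stove use, households that use both kinds of stove would overlap more with controls, and the SE would grow less than in the simulation.

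Third, the covariate that is firmly named, malaria, carries little weight numerically, and nothing in the article shows that the arms will differ in it. That stands. It limits the harm but does not make a variable measured at birth a baseline covariate.

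Fourth, a reader might fault the article for not naming the lead model. That choice is commonly left to a statistical analysis plan, which is not at hand, so it is no part of this point.

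**Conclusion.** The point holds for the adjusted intention-to-treat estimates only. As written, the birth-weight model conditions on a variable measured after weeks of intervention, and the wording on stove use allows the intervention's own mechanism into the models for both main outcomes.

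For placental malaria the distortion is small: at most about 0.04 SD under assumed differences of up to 10 points in prevalence and 0.4 SD in effect, and about zero if the arms do not differ. For stove use, if it is entered, the arm effect is pulled towards zero in proportion to the share that runs through use, and its SE grows, roughly doubling under the use levels assumed here.

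A reader might infer that stove-use adjustment would turn a benefit into an apparent harm. The article does not support that as a prediction. It takes a strong link between use and an unmeasured cause of birth weight together with accurate reporting, and moderate error in a questionnaire measure brings the estimate back above zero in the case worked here.

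**What to change.** Amend the Analysis plan so that covariates in the adjusted intention-to-treat models are limited to those fixed before stove delivery: maternal, household and community characteristics, and gestational age at enrolment. State that stove use will not enter those models, and change the Discussion sentence to match. Use placental malaria and stove use only in exposure-response, adherence or mediation analyses that are labelled as such.

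This takes a sentence or two and no new data. The article reports that recruitment was still under way, so the change could precede analysis of outcomes. The cost is the small precision gain that placental malaria would have brought to the adjusted birth-weight model.

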### Trial monitoring

GRAPHS has an external advisory committee with five members who were chosen for their expertise and for their ability to help disseminate study findings.

A Data and Safety Monitoring Board (DSMB) with four members with expertise in household air pollution, in statistics, and in trial management has been convened to advise regarding any safety issues and review final results. There are no interim analyses planned. Both committees meet periodically to review trial developments. Since the trial does not involve any drugs or medical procedures, the DSMB is not carrying out any interim analyses.

### Consent and ethical approval

We obtain informed consent from each participant prior to enrollment. The study has received unconditional approval by the Institutional Review Board at Columbia University Medical Center, the Ghana Health Service Ethical Review Committee, the Kintampo Health Research Centre Institutional Ethics Committee, and the Partners Human Research Committee. The study is registered with clinicaltrials.gov (NCT01335490).

## Discussion

Household air pollution exposure is a major health risk that requires well-tested interventions. GRAPHS evaluates the efficacy of both clean fuels (LPG) and efficient biomass cookstoves vis-à-vis birth weight and physician-assessed severe pneumonia incidence in the first year of life. The study is set up to provide relevant health outcome data for energy policies in developing countries.

GRAPHS is particularly policy-relevant in Ghana, as it comes at a time when the Ghana government has increased efforts to promote both clean biomass cookstoves and LPG. Spurred in part by the start of domestic LPG production from offshore oil fields, Ghana has recently made a major, public commitment to reduce dependence on uncontrolled combustion for cooking. These commitments appear to be leading to concrete steps to promote LPG access throughout the country and to develop supply chains and subsidies for efficient biomass cookstoves in rural areas. These activities are occurring against a backdrop of a very high burden of disease from HAP. Indeed, the recent Global Burden of Disease/Comparative Risk Assessment process concluded that household air pollution is the most impactful of the modifiable risk factors evaluated for Ghana [31].

We are hopeful that our research will inform these efforts, and similar efforts that are currently underway in other countries, in three ways. First, GRAPHS will provide concrete evidence on the health benefits both from efficient cookstoves and from LPG. These data will provide valuable inputs for benefit-cost analysis of proposed rural energy policies that promote clean cooking. In particular, the direct comparison of LPG to efficient cookstoves will help policy-makers evaluate whether the health benefits of LPG justify its higher cost. Second, our study will help clarify the feasibility and health ramifications of interventions that target pregnant women. Ghana, like most developing countries, has systems in place to reach pregnant women with specific interventions. Third, GRAPHS has built capacity in Ghana for future evaluations of the health implications of energy policies.

### Selecting intervention cookstoves

A central challenge in designing household energy intervention studies is the choice of intervention. To deliver health benefits, interventions must be clean – though as noted above we do not yet know how clean is clean enough – and acceptable to users. Furthermore, if interventions are to be relevant to public health interventions beyond the research program, they must be accessible to the poor. This means that they must be either very inexpensive, or they must be aligned with broader public policy goals and, therefore, plausible targets for subsidies and other government programs.

Our original proposal to National Institute of Health for funding called for the use of locally available rocket stoves. This approach grew out of our unpublished pilot work that showed that such stoves could reduce exposures by approximately 50 %; similar estimates for Ghana have been published by another group [32]. After receiving the grant and convening our external advisory committee, we came to believe that this exposure reduction was unlikely to result in detectible changes in health outcomes. In particular, preliminary exposure response data from the RESPIRE trial [13] suggested that a 50 % exposure reduction would require a sample size approximately twice that which we were funded to study.

This observation prompted a long search for an alternative intervention. We piloted industrially produced rocket stoves, but found that they performed no better than the made-in-Ghana variant. We evaluated the Philips Cookstove (Royal Philips, Amsterdam, The Netherlands), which can be very clean thanks to forced-draft combustion [33], but ultimately rejected it because it requires an external power source to charge its battery and also because its top-loading design seemed incompatible with Ghanaian cooking practices. The BioLite HomeStove appeared to address both of these issues – its thermoelectric system provides electricity for forced draft combustion without a grid connection, and its stable, side-loading design emulates the rocket stoves that we had successfully piloted. We initiated discussions with BioLite in 2010, but at that time they were still developing their technology.

We also started investigating an LPG intervention. LPG is very clean [33] and very convenient, but we were uncertain of its public health relevance given its high cost and limited availability in Ghana. In 2012 we learned, however, that Ghana had laid plans for a substantial program to increase access to LPG both in rural and urban areas [34] and that Ghana’s Ministry of Energy had initiated a “Rural LPG Program” that was delivering free cookstoves and subsidized gas to rural communities. This support from the government was sufficient to convince the GRAPHS team that LPG was indeed a germane alternative.

We remained convinced, however, of the need to include an efficient biomass arm. While our interactions with the Government of Ghana had persuaded us that LPG was worth testing, we remained hopeful that efficient biomass combustion would provide a substantially less costly intervention for future large-scale interventions. Between 2010 and 2012 BioLite developed a production model of their HomeStove, and we began pilot testing in spring 2012. Initial units proved unreliable, but after several iterations we were satisfied that the BioLite was robust to long-term use. We launched enrollment in fall 2013 when the first shipment of BioLite stoves reached our study area in Ghana.

Our intervention entails providing participating households with clean cookstoves and, in the case of the LPG intervention, with an adequate supply of fuel. As with many public health interventions, we cannot ensure perfect compliance. While we try to minimize use of the traditional three-stone fires in intervention households through weekly stove use encouragement visits, we have observed that many households continue to use traditional stoves for certain cooking tasks (a practice sometimes referred to as “stove stacking” [35]). We address this in three ways. As discussed below, we are currently undertaking a separate study to objectively quantify stove use across arms and to link it to household characteristics. Additionally, we carry out weekly questionnaire-based assessments of stove use; these data will be available as a covariate in our adjusted analyses of our main health outcomes. Third, we collect extensive personal exposure data, which capture emissions both from continued use of incumbent stoves and from other nearby sources. These data will be used to estimate exposure-response relationships for our main outcomes.

